### Secondary outcomes

The secondary outcomes in this trial include blood drug levels, immunological outcome, clinical outcome, patient satisfaction with the system, and the system stability and cost-effectiveness. The trough levels of tacrolimus and mycophenolic acid, creatinine level, and eGFR are measured at 4, 8, 12, 16, 20, and 24 weeks of follow-up. PRA is assessed at baseline and 24 weeks, and serum BK virus at 12 weeks. For clinical outcome evaluation, biopsy-proven acute rejection (BPAR) and graft loss developing during the follow-up are monitored. The patient Satisfaction Questionnaire is filled out at 4 and 24 weeks in the ICT-based centralized clinical trial monitoring group in order to assess how well the patients are satisfied with the system-enabled adherence management. The malfunction rate of the ICT-based centralized monitoring system is checked as well as any discrepancy between the smart pill box record and the patient-kept drug administration diary. Information about patients’ medication use sent to the ICT-based monitoring system is compared with the daily records of medication use written by the patients (type of medications used, number of pills ingested, and time of ingestion) to assess how closely they match. Stability is measured by using the following equation:$$ \frac{\mathrm{Number}\  \mathrm{of}\  \mathrm{pills}\  \mathrm{taken}\  \mathrm{over}\ \mathrm{a}\ \mathrm{certain}\  \mathrm{period}\  \mathrm{according}\  \mathrm{to}\  \mathrm{the}\ \mathrm{ICT}\hbox{-} \mathrm{based}\  \mathrm{centralized}\  \mathrm{monitoring}\  \mathrm{system}}{\mathrm{Number}\  \mathrm{of}\  \mathrm{pills}\  \mathrm{prescribed}\  \mathrm{over}\  \mathrm{the}\  \mathrm{sampling}\  \mathrm{period}\  \mathrm{according}\  \mathrm{to}\  \mathrm{the}\  \mathrm{daily}\  \mathrm{record}\  \mathrm{of}\  \mathrm{medication}\ \mathrm{use}}\times 100\%. $$

Cost-effectiveness evaluation parameters include installation of the ICT-based centralized monitoring system, additional hospitalization due to non-adherence, ambulatory tests, and trips for hospital visits. The expenses of the ICT-based centralized monitoring system will consist of the price of the pill box itself, and the costs for transferring medication use information to the home monitoring system and the eCRF system. In cases in which patients develop acute adverse reactions due to irregular medication use and are hospitalized, receipts of the hospitalization fee, outpatient clinic visit fees, and transportation fees will be collected. We will compare differences in the ICT-based centralized monitoring system expenses, additional hospitalization fees, outpatient clinic examination fees, and transportation fees between the two groups.

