**Fig. 1 Fig1:**
[figure not shown]
ICT-based study design. *ICT* information and communication technology, *R* randomization, *S* screening, *W* week

Both groups are to make six office visits after randomization at 4, 8, 12, 16, 20, and 24 weeks. Each visit requires measurement of blood drug level, creatinine level, and estimated glomerular filtration rate (eGFR). Serum BK virus is assessed at 12 weeks, and panel reactive antibody (PRA) at 24 weeks. Both groups keep a drug administration diary that specifies date, whether a dose is taken or not, dosing time, and dosage. At each visit, subjects go over the diary with investigators and fill out a questionnaire using the Modified Morisky Adherence Scale [12]. The ICT-based centralized clinical trial monitoring group completes a patient Satisfaction Questionnaire developed by the ICT Clinical Trial Support Center at 4 and 24 weeks. The system Satisfaction Questionnaire can be found in Additional file 1. The protocol flow is shown in detail in the Standard Protocol Items: Recommendations for Interventional Trials (SPIRIT) figure in Fig. 2. A SPIRIT Checklist is provided in an Additional file 2.

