### The ICT-based centralized clinical trial monitoring system: feedback

In the ICT-based centralized monitoring group, both subjects and medical staff receive feedbacks regarding a missed dose, misuse, and overuse of the medication in the form of a text message alarm. In case of a missed immunosuppressant dose, the first violation generates a feedback within 1 h at the break of the ± 3-h range from the fixed dosing time. Up to two additional texts are sent at an interval of 30 min if the dose is still not taken after the feedback. For any discrepancy between the dosage taken and the dosage prescribed, a feedback is sent within 1 h from the moment of recognition. Similarly, if a dose is taken outside of the allowed ± 3-h dosing time range, a feedback is sent within 1 h of recognition. To minimize reminder fatigue, we limited additional alarms after the first feedback to two times. Any additional alarms after the two reminders will be sent to the patient’s family. Medication use information of KTRs is sent to the home monitoring system and the eCRF system in real time to allow the medical staff to check on the patients’ medication use, dosing time, and dosage. Through the eCRF system, medical staff can gain insights into all patients’ daily history of medication use, and all patients’ or a single patient’s monthly history of medication use.

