### Primary outcomes

The primary outcome in this trial is adherence to medication. Both in the ICT-based centralized clinical trial monitoring group and the control, pill counts are done at 4, 8, 12, 16, 20, and 24 weeks of follow-up. Multiple items of adherence – dose-taking compliance, dose-frequency compliance, dose-interval compliance, and drug holidays – are assessed based on the smart pill box data in the ICT-based centralized monitoring group and the drug administration diary in the ambulatory follow-up group, respectively. In the ICT-based centralized monitoring group, three types of immunosuppressants—tacrolimus, mycophenolic acid, and steroids—are placed in a single bag, which is then placed inside a smart pill box. The patient’s medication usage is assessed based on the perceived weight of the leftover medications in the bag. On the basis of this weight information, we can identify the type and dose of medications that the patient has ingested, and calculate the adherence. Each item of adherence is listed below [15]:Dose-taking compliance = the number of pills taken over a certain time period/the number of pills prescribed over the same period × 100%Dose-frequency compliance = the number of days of correct daily dosing frequency over a certain time period/the number of days over the same period × 100%Dose-interval compliance: the number of correct dosing interval over a certain time period/the number of days over the same period × 100%.A correct dosing interval is defined with a ± 25% margin (in this trial, medication is taken twice a day, with a dosing interval of 12 h. Allowed dosing interval is thus ranged from 9 to 15 h)Drug holidays = the number of days without dose taking/the number of days over the same period × 100%Medication possession ratio = the sum of the days’ supply for all fills of a given drug in a particular time period/the number of days in the time period × 100%

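### The box–diary agreement can be overstated, because the diary is open to the box's own feedback and the visit pill count is not used as a second check

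*Protocol article*

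**What the plan says.** All places are in the protocol article.

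- **Secondary outcomes.** The plan checks "any discrepancy between the smart pill box record and the patient-kept drug administration diary". Box data on drug type, pill number and time of intake are set against the patient's own daily records "to assess how closely they match". The diary is the only reference named. The section also gives a malfunction rate and a stability equation, which divides pills taken according to the system by pills prescribed.
- **Study design.** "Both groups keep a drug administration diary that specifies date, whether a dose is taken or not, dosing time, and dosage". The hour of entry is not given. The section adds: "At each visit, subjects go over the diary with investigators".
- **Feedback section.** In the ICT arm "both subjects and medical staff receive feedbacks regarding a missed dose, misuse, and overuse of the medication in the form of a text message alarm". On amounts: "For any discrepancy between the dosage taken and the dosage prescribed, a feedback is sent within 1 h from the moment of recognition". A missed dose triggers a text within 1 h after the ±3-h window closes, with up to two repeats. Box data reach staff in real time through the eCRF.
- **Smart pill box.** The patient can check what is left in the box.
- **Primary outcomes.** In both arms "pill counts are done at 4, 8, 12, 16, 20, and 24 weeks of follow-up". No section uses these counts to check the box.

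**The concern.** An accuracy check needs a reference obtained without knowledge of the reading being checked. Here the patient, who writes the reference, and the staff, who review it, both have access to the box's reading. If the box wrongly reports a missed or wrong dose, the patient is told so and may doubt or change a correct entry. The discrepancy that should have exposed the box's error then disappears.

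Stability of the system is in the title and among the aims. Box data also supply the ICT arm's adherence measures under Primary outcomes, where use is inferred from the weight of three drugs in a single bag. Overstated agreement would lend that instrument credibility it has not earned.

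**Working it through.** **1. Who can see the box reading before the diary is final?**

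| Box event | Text to patient | Other access |
|---|---|---|
| Dose taken correctly, box reads it as missed, wrong amount or mistimed | Yes | Patient sees stock; staff see box data |
| Dose missed or wrong, box reads it as correct | No | Patient sees stock; staff see box data |
| Dose and box reading both correct | No | Same |

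The text route reaches the box's false alarms. Errors that hide a real deviation can reach the diary only through the display or the staff review.

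**2. Could the entry follow the text?** For a dose taken on schedule but read as missed, the text cannot come until the 3-h margin has passed. An entry made at dosing precedes it. An end-of-day entry for a morning dose follows it. The article allows both.

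**3. Illustration of direction.** The article gives no error rates, so every input below is an assumption, and only taken/missed status is modelled. Let m be the share of doses missed, a the share of taken doses the box reads as missed, b the share of missed doses it reads as taken, g the share of missed doses the diary records as taken, h the share of taken doses the diary records as missed, and c the share of entries with box missed and diary taken that are changed to match the box.

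With m = 0.05, a = 0.05, b = 0.02, g = 0.30, h = 0.005:

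- Both taken: 0.95 × 0.95 × 0.995 + 0.05 × 0.02 × 0.30 = 0.8983
- Both missed: 0.95 × 0.05 × 0.005 + 0.05 × 0.98 × 0.70 = 0.0345
- Box missed, diary taken: 0.95 × 0.05 × 0.995 + 0.05 × 0.98 × 0.30 = 0.0620
- Agreement = 0.8983 + 0.0345 + 0.0620c

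Twice-daily dosing over 24 weeks gives 24 × 7 × 2 = 336 doses per patient. The last column covers all combinations of m = 2, 5 or 10%, a = 2 or 5%, and g = 30 or 60%, with b = 2% and h = 0.5%.

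| c | Agreement, this example | Discrepancies per 336 doses | Agreement (kappa), all combinations |
|---|---|---|---|
| 0 | 93.3% | 22.6 | 89.1–97.0% (0.18–0.69) |
| 0.25 | 94.8% | 17.4 | 91.7–97.6% (0.46–0.77) |
| 0.5 | 96.4% | 12.2 | 94.3–98.2% (0.67–0.85) |
| 0.9 | 98.9% | 3.8 | 98.5–99.2% (0.89–0.95) |

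The box is identical in every row. Its true accuracy in this example is 0.95 × 0.95 + 0.05 × 0.98 = 95.2%. Agreement exceeds that only once c passes (0.9515 − 0.9328)/0.0620 = 0.30. Below that, diary errors keep agreement under the true accuracy.

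**4. The printed equation.** It divides by pills prescribed. Taking one pill per dose, a box total of 280 out of 336 prescribed gives 280/336 = 83.3%, whether the diary shows 280 or 336 taken. Changed intake entries do not move it.

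**The case against.** The strongest reply is that the order of events is not documented. The article calls the diary a daily record and gives no hour of entry. It says the diary is gone over with investigators, not that entries are altered or that the box log is open at the time. Rules on diary completion and locking may stand in the full protocol. This is right, and a reader who inferred that entries are written after the text, or corrected to the box at the visit, would be going beyond the text. It does not restore independence, however. The texts are part of the intervention itself, and the article states that patient and staff receive them.

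Second, a text may correct a genuine diary error, and such errors lower agreement for reasons unrelated to the box. This stands, and the crossover at c = 0.30 shows it. The net bias against true accuracy is undetermined. What holds is that any change toward the box raises agreement without improving the box.

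Third, the Background section rates pill counts as less reliable than other methods, chiefly for dosing time. A net count over four weeks cannot check individual doses, and opposite errors cancel. The count can therefore supplement the diary but not replace it. It may also not yet be independent: remaining pill counts are listed among the box's own outputs, and Primary outcomes does not say how the visit count is made.

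**Conclusion.** The point holds as a risk, not as a demonstrated bias. The diary is not an independent reference for the box, and agreement on drug type, pill number and time can be overstated, especially for doses the box wrongly flags. The size cannot be derived from the article. It depends on how often entries are changed, which is unknown and could be zero.

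A reader might infer that the stability assessment as a whole is inflated, whatever measure is used. The documents do not support that. The equation as printed does not use diary intake, and the malfunction rate is not said to rest on the diary. The exposure is confined to the match and discrepancy comparison, which is one part of the secondary outcomes. The sample size and the planned test of adherence between the arms are unaffected. The remedy is cheap and worth making.

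**What to change.** Amend Secondary outcomes, with matching visit wording:

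- **Quantity.** Add the visit pill count, counted by hand and not read from the box, as a second and independent check alongside the diary. For each 4-week interval, compare pills the box recorded as removed with pills supplied minus pills returned.
- **Drug type and time.** Use the diary as entered before box data are opened or discussed at that visit. Record later corrections separately.
- **Reporting.** Tabulate agreement separately for doses with and without a feedback text. The first group is the one most open to contamination by text.

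The cost is some visit-procedure wording and one more table, since diaries, texts and pill counts are already part of the trial. If ICT-arm counts are currently read from the box, a brief hand count at each of the six visits is new work. Entering the diary before box data are opened at the visit does not undo the effect of texts already received, which is why the split table is needed as well.

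### The stability equation divides by pills prescribed instead of pills taken per the diary, so it repeats dose-taking compliance and cannot show box-diary agreement

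*Protocol article*

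**What the plan says.** All references are to the protocol article.

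- **Secondary outcomes, purpose.** Besides the system's malfunction rate, the trial checks "any discrepancy between the smart pill box record and the patient-kept drug administration diary". The comparison of system data with diary data covers "type of medications used, number of pills ingested, and time of ingestion) to assess how closely they match".
- **Secondary outcomes, formula.** The next sentence begins "Stability is measured by using the following equation". The numerator is the number of pills taken according to the ICT system. The denominator is the number of pills prescribed according to the daily record of medication use. The ratio is multiplied by 100%.
- **Primary outcomes.** Dose-taking compliance is "the number of pills taken over a certain time period/the number of pills prescribed over the same period", times 100%. The adherence items "are assessed based on the smart pill box data in the ICT-based centralized monitoring group".
- **Study design, text after Fig. 1.** "Both groups keep a drug administration diary that specifies date, whether a dose is taken or not, dosing time, and dosage". A prescribed pill count is not among the listed contents.

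**The concern.** The narrative and the equation describe different quantities. Agreement between two records needs both records of the same event, here pills taken per the box and pills taken per the diary. The equation uses only the box record of pills taken and sets it against the prescription.

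Stability appears in the article's title and in its stated aims. It also bears on how the adherence comparison is read, because adherence comes from the box in one arm and from the diary in the other. The ICT arm keeps both records, so box-diary agreement there is the direct check on how far the two sources differ. An analyst who follows the printed formula would report a number called stability that moves with patient behaviour and leaves that question unanswered.

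**Working it through.** The document states no stability value or threshold, so there is no figure to reproduce. The check compares the definitions and then evaluates them on assumed counts.

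**Notation, per ICT-arm patient over one period**

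- P = pills prescribed
- B = pills taken per the box
- D = pills taken per the diary

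**Step 1: term by term**

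| Measure | Numerator | Denominator |
|---|---|---|
| Dose-taking compliance, ICT arm (Primary outcomes) | B | P |
| Stability as printed (Secondary outcomes) | B | P |
| What the narrative compares (Secondary outcomes) | B | D |

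The first two rows are the same, provided that the periods coincide and the diary-based prescribed count equals the prescription.

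**Step 2: what the printed ratio contains**

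B/P = (B/D) × (D/P)

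That is, printed stability equals the box-diary ratio multiplied by diary-reported adherence. Even when B = D, it equals D/P and still varies with adherence.

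**Step 3: illustrative counts with P = 100 (assumed, not from the document)**

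| Case | B | D | Printed, B/P | Box/diary, B/D |
|---|---|---|---|---|
| Perfect agreement | 80 | 80 | 80% | 100% |
| Perfect agreement | 85 | 85 | 85% | 100% |
| Perfect agreement | 95 | 95 | 95% | 100% |
| All pills taken, box misses 15, diary correct | 85 | 100 | 85% | 85% |
| Box 10 below diary | 80 | 90 | 80% | 80/90 = 88.9% |
| Box 20 above diary | 100 | 80 | 100% | 100/80 = 125% |

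Rows 2 and 4 have the same printed value, 85%, although the records agree fully in one and differ by 15 pills in the other. The last row prints 100% although the records differ by 20 pills. The decomposition checks: 1.25 × 0.80 = 1.00, and 0.889 × 0.90 = 0.80.

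**Step 4: what a ratio of totals still hides once the denominator is corrected**

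Assume 100 one-pill dose slots: 80 recorded as taken by both sources, 10 by the diary only and 10 by the box only. Then B = 90 and D = 90, so B/D = 100%. Dose-level agreement is 80/100 = 80%. The ratio of totals also ignores drug type and time, both of which the narrative says are compared.

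**The case against.** The best defence is that this is a slip of wording. The denominator refers to the daily record, the listed diary contents concern doses taken, and the preceding sentence speaks of pills ingested. Together these suggest that pills taken per the diary was intended. That reading is plausible, and it is a reason why the repair is small. It does not correct the printed term, which a programmer or analyst would follow.

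A reader might infer more than the document supports, in three ways:

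- **That the trial could not conclude on stability at all.** It could. The malfunction rate and the comparison of box and diary are stated separately and do not depend on the equation.
- **That a faultless system would be declared unstable.** The article gives no threshold, pass mark or test for stability. The ratio is a descriptive percentage.
- **That the ratio measures adherence and nothing else.** It does respond to recording error, as the fourth row of the table shows. The fault is that it cannot separate such error from missed doses.

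It can also be said that the choice of agreement index is detail for the full protocol or analysis plan. That is fair for the dose-level index, which is therefore an addition rather than a requirement. It does not cover the denominator, which the article states explicitly. Finally, the corrected ratio does not isolate device error either, because the diary may be wrong. This stands, and it limits how the result may be described.

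**Conclusion.** The concern holds in a bounded form. The printed stability equation contradicts the purpose given in the sentence before it and, for an ICT-arm patient, reproduces dose-taking compliance. With perfect box-diary agreement it returns the adherence percentage (85% at 85% adherence), and it can return 100% when the two records differ. As a named measure it cannot show agreement.

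The reach is one secondary outcome in one arm. The primary comparison, the sample size, the malfunction rate and the narrative discrepancy check do not depend on it, and no data are lost, because box and diary are both recorded.

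The identity with dose-taking compliance assumes a common period and the same prescribed count in both formulas. The percentages are illustrations of what can happen. The document gives no basis for estimating how large the distortion would be in this trial.

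**What to change.** 1. **Required.** In the denominator of the stability equation, replace pills prescribed with pills taken according to the diary, and use one period for numerator and denominator (the equation words the two periods differently).
2. **Preferable.** Also report dose-level agreement: scheduled doses on which box and diary agree (taken or not, number of pills, time within a stated tolerance), divided by all scheduled doses with both records, × 100%. This prevents over- and under-counts from cancelling and covers the timing that the narrative promises to compare. Drug type can be tabulated alongside.
3. **Interpretation.** Describe the result as agreement between box and diary, not as device accuracy, and keep the malfunction rate as a separate measure.

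The cost of item 1 is a change of wording before analysis. Item 2 needs a stated time tolerance and some programming. Both use data already collected in the ICT arm.

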### Study design

This study has a multicenter, open-label, prospective, randomized controlled trial (RCT) design. One hundred fourteen KTRs who fill out the Informed Consent Form are registered and randomized 1:1 into the ICT-based centralized clinical trial monitoring group (*n* = 57) or the ambulatory follow-up group (*n* = 57). The planned follow-up duration is 6 months (Fig. 1). The ICT-based centralized clinical trial monitoring group is given a smart pill box equipped with a personal identification system. Fingerprint registration is required in advance, so that it would be used for authentication before each use of the smart pill box later. The adherence-related information obtained from the pill box is saved, monitored, and sent out via a home monitoring system. Of the home monitoring system data, those necessary for the clinical trial are extracted and incorporated into the electronic Case Report Form (eCRF) system. All data is consolidated and managed within the comprehensive clinical trial management system (CTMS). In the ICT-based, centralized clinical trial monitoring group, feedback is sent to both patients and medical staff in the form of texts and pill box alarms if there is a dosage/dosing time error or a missed dose.

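### Tying cost receipts to admissions attributed to irregular medication use leaves the cost comparison open to differential attribution, and the two statements of the ICT cost do not agree

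*Protocol article*

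**What the plan says.** All the cost text is in the protocol article, Secondary outcomes.

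- **Parameters.** The list opens "Cost-effectiveness evaluation parameters include installation of the ICT-based centralized monitoring system" and continues with "additional hospitalization due to non-adherence, ambulatory tests, and trips for hospital visits". The causal condition is attached to hospitalisation; tests and trips carry none.
- **Collection.** The condition is "In cases in which patients develop acute adverse reactions due to irregular medication use and are hospitalized"; in those cases "receipts of the hospitalization fee, outpatient clinic visit fees, and transportation fees will be collected". No other receipt collection is described.
- **ICT expenses.** These "will consist of the price of the pill box itself, and the costs for transferring medication use information" to the home monitoring and eCRF systems.
- **Comparison.** System expenses and the hospital, outpatient and transport fees are then compared between the two groups.

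Elsewhere, Study design states: "This study has a multicenter, open-label, prospective, randomized controlled trial (RCT) design". The section on feedback says that in the ICT arm "both subjects and medical staff receive feedbacks regarding a missed dose, misuse, and overuse", and that staff can check use, timing and dosage in real time. In both arms, Study design and Primary outcomes provide diary review, the Modified Morisky scale, drug levels and pill counts at the six visits.

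**The concern.** Whether an admission enters the cost comparison depends on a judgement, made after randomisation, that irregular medication use caused it. Irregular use is what the intervention is meant to change, and it is documented more closely in one arm. The same admission could be counted in one arm and missed in the other. Randomisation protects a comparison of all costs; it does not protect a comparison of costs selected in this way.

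The condition may also miss relevant costs. As worded, an outpatient visit prompted by an alert in a patient who is never admitted produces no receipt.

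On the intervention side, one sentence counts installation and the next itemises the expenses without it. Staff time spent on alerts appears in neither. If the shorter list is applied literally, the ICT cost may be too low.

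Cost-effectiveness is a stated study objective. An analysis plan written later could not repair the collection rule, because receipts not gathered during follow-up are hard to recover.

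**Working it through.** **Plan's own figures.** The article gives no cost, admission rate or cost difference, so there is no cost figure to reproduce. The only design figure used here is 57 per arm (Sample size): 51/(1 − 0.10) = 56.7, rounded up to 57. The point does not depend on it.

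**Step 1: information available for attribution.**

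| Source | ICT arm | Control arm |
|---|---|---|
| Diary, pill count, drug level, Morisky scale at visits | yes | yes |
| Continuous box data on dose and time | yes | no |
| Alerts to staff | yes | no |

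Control attribution thus rests on several visit-based measures. The difference between arms is the continuous record, available to staff who are not blinded by design.

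**Step 2: size of a false difference (illustration; all rates assumed).** Let h be the true all-cause admission risk, equal in both arms, and a the share of admissions attributed to irregular use. Counted admissions per arm = 57 × h × a, so the false difference (ICT minus control) = 57 × h × (a_ICT − a_control).

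| h | Admissions per arm | Counted, control (a = 50%) | Counted, ICT (a = 25%) | False difference |
|---|---|---|---|---|
| 5% | 2.85 | 1.43 | 0.71 | −0.71 |
| 10% | 5.70 | 2.85 | 1.43 | −1.43 |
| 20% | 11.40 | 5.70 | 2.85 | −2.85 |

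Swapping the shares reverses the sign. Shares of 30% in control and 20% in ICT give about −0.3 to −1.1 over the same range of h. Equal shares give zero. Either direction is plausible: box data may reveal irregular use that visits miss, or may rule it out where control staff would suspect it.

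**Step 3: the two statements of ICT cost.** The parameter sentence names installation. The itemising sentence is worded as a complete list, box price plus data transfer. Either installation is meant to fall within those two items, or it has been left out. The text does not settle which.

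**Step 4: possible staff time (illustration; alert rate and minutes assumed).** Twice-daily dosing (Primary outcomes) over 24 weeks gives 2 × 168 = 336 dosing times per patient.

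- Low: 336 × 2% = 6.7 alerts; at 2 minutes each, 0.22 hours per patient; × 57 = 12.8 hours for the arm.
- High: 336 × 10% = 33.6 alerts; at 10 minutes each, 5.6 hours per patient; × 57 = 319.2 hours for the arm.

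This matters only if the costing perspective includes the provider, and no perspective is stated.

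**The case against.** The strongest reply is that much of the criticism could be read out of silence.

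- The article does not say that receipts are collected in no other case, and it lists ambulatory tests and trips without a causal condition. It names neither the person who attributes cause nor whether that person is blinded. The full protocol, not shown, may settle these points.
- Control staff have pill counts, drug levels and a questionnaire at every visit as well as the diary, so differential attribution is possible but not demonstrated.
- Installation may be a label that the next sentence merely itemises.
- The feedback section prescribes no staff action or time per alert. Collecting patients' fee and travel receipts would fit a patient or payer perspective, under which staff time need not be costed.
- An incremental ratio or a bootstrap interval is ordinary analysis-plan content.

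Most of this stands and limits the point. A reader might infer that the comparison is biased in a known direction, that control attribution rests on the diary alone, or that the ICT cost is certainly too low. The documents support none of these. What the reply does not remove is the stated trigger: receipts are linked to a causal judgement, the resulting fees are compared between arms, and no collection independent of cause is described.

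**Conclusion.** The point holds as a vulnerability in data collection. The hospital, outpatient and transport cost comparison is open to differential attribution of unknown direction and size. On assumed admission risks of 5% to 20% and attributed shares of 50% and 25%, the false difference is 0.7 to 2.9 counted admissions in either direction; it is zero if the shares are equal. The conclusion rests on reading the receipt condition as the operative rule, since no other is described.

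The ICT cost may be understated by an amount the documents do not allow one to determine, because the sentence naming installation and the sentence itemising expenses do not match. Whether staff time belongs in the cost depends on the unstated perspective.

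The absence of a ratio or interval is not a fault of this article. Neither the primary outcome nor the sample size is affected. The change is worth making because it is cheap and because the data cannot readily be recovered later.

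**What to change.** 1. Collect hospitalisation, outpatient and travel costs in both arms from randomisation to week 24, regardless of cause. Keep attribution to non-adherence as a descriptive split of those costs.
2. Reconcile the itemised ICT expenses with the installation parameter, so that one list states what is counted.
3. State the costing perspective. If it includes the provider, add staff time spent on alerts.

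The form of the cost-effectiveness analysis can be left to the analysis plan.

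**Cost.** More receipts to gather, which can be done at the existing visits, and a simple estimate of alert-handling time if item 3 requires it. Unrelated admissions will add variance to the cost difference, so with 57 per arm the estimate will be less precise; the attributed split remains available for description. The trial was already running when the article was submitted, so receipts for earlier events may have to be sought retrospectively.
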